### Controls (second-line systemic chemotherapy)

Patients randomised to receive further chemotherapy (chemotherapy alone) will commence treatment within 6 weeks after sMDT or 4 weeks after randomisation, whichever is sooner. The second-line chemotherapy regime will be selected at the discretion of the treating oncologist and will adhere to NICE guidelines and local protocols.

### Outcomes

The primary objective of the LAP-PIE trial is to ascertain feasibility of such a trial concept. In particular, the ability to identify and recruit LAPC patients at the selected sites to the LAP-PIE trial will be evaluated. The primary outcome consists of recruitment rate, number of screening failures, number of patients completing study pathway as per protocol and trial withdrawal rate.

The secondary objectives of the LAP-PIE trial aim to assess the practicality and technical success rate of pancreas IRE treatment. Technical success will be determined by the interventional radiologist performing the procedure. The procedure will be deemed to be technically successful if the entire tumour has been treated based on imaging performed during the intervention. Completion and complication rates of IRE procedures will be evaluated. The proportion of patients in whom percutaneous IRE was successful, defined as no local growth on follow-up, will be determined as will the proportion of patients who became eligible for surgery following IRE and the R0/R1 resection rates in these participants. Acceptability of pancreas IRE therapy to patients and their clinicians, rate of withdrawal from the study and outcome measures including OS (measured from randomisation), PFS and QoL will be evaluated. Finally, health-related costs, including indicative costs related to health resource use in both arms, social costs of attending IRE treatment such as cost of travel to and from a tertiary centre, time off work and social support costs will be evaluated.

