### Repeat staging after first-line chemotherapy and possibility of resection

Staging is repeated following first-line chemotherapy for LAPC and imaging is reviewed once again regarding suitability for resection. In patients with locally advanced disease undergoing first-line treatment with FOLFIRINOX, 25.9% underwent resection, with an R0 resection rate of 78.4%; however, the long-term outcomes for these patients are not reported in the studies, and there is still a possibility of recurrence although at later date.^11^

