## Methods and analysis

### Study design and setting

The LAP-PIE trial is a UK multicentre feasibility study that will recruit 50 patients with LAPC in whom the disease has remained localised and unresectable following FOLFIRINOX. Patients will receive 3–6 months of FOLFIRINOX prior to restaging and being assessed for study eligibility. All participants will be offered palliative chemotherapy according to standard centre protocols and half will also be offered one IRE procedure. If new agents for second-line therapy are approved by NICE prior to or during the LAP-PIE trial, these can be offered in the second-line chemotherapy arm and following IRE therapy if considered appropriate by the treating oncologist. Patients randomised to the control arm who have benefitted from initial chemotherapy with FOLFIRINOX may continue on the same regimen if this deemed appropriate by the treating oncologist. It is an open-label study. Patient enrolment is expected to last 15 months assuming a recruitment rate of 0.8 patients per site per month across seven UK centres and an opening site rate of 0.5 per month. The trial will be conducted in specialist pancreas cancer centres. IRE will be delivered across all trial centres. Interventional radiologists performing pancreas IRE in the trial will have performed a minimum of five previous pancreas or liver IRE ablations prior to administrating IRE to participants enrolled in the trial. Additional technical support will be available from manufacturers of the equipment, AngioDynamics. Figure 1 summarises the trial design and table 1 demonstrates the schedule of enrolment, interventions and assessments.

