The intraoperative imaging will be reviewed by the lead radiologist at each site and if the entire tumour has been treated based on these images, the procedure will be deemed as successful. The technical success will be confirmed by central review. Contrast CT follow-up scans will be assessed for evidence of tumour growth as indicated by mass enlargement or increased vascularity. In the absence of tumour growth, the procedure will be considered successful at follow-up. At the end of the follow-up period, serial imaging will be analysed, and the tumour staged. Local disease control will be evaluated according to the Response Evaluation Criteria in Solid Tumours. This will be performed by the radiology leads at each site and confirmed by a central review.

Following IRE, patients in this arm will be offered second-line chemotherapy, which is the current standard of care. The drug choice and timing of chemotherapy will be decided by treating oncologists and will adhere to NICE guidelines.

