### Follow-up

All patients will be clinically reviewed every 3 months during which a CT CAP will be performed. Additional imaging can be performed if clinically indicated. Other investigations will include biochemistry and haematology, CA19–9 levels, C Reactive Protein (CRP), QoL as measured by a validated questionnaire (EQ5D-5L)^28^ and a clinical review of any AEs experienced. This information will be recorded in an electronic case report form.

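### Local control, eligibility for surgery and R0/R1 resection are defined only after IRE, so the single-arm rates cannot separate IRE from chemotherapy and a randomised comparison goes unused

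*Protocol article*

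**What the plan says.** The Outcomes section defines local success as "The proportion of patients in whom percutaneous IRE was successful, defined as no local growth on follow-up". In the same sentence it adds "the proportion of patients who became eligible for surgery following IRE and the R0/R1 resection rates in these participants". Both are worded for patients who have had IRE.

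The Pancreas IRE section has the matching rule, "In the absence of tumour growth, the procedure will be considered successful at follow-up", and then "Local disease control will be evaluated according to the Response Evaluation Criteria in Solid Tumours". Both sentences stand under the intervention heading. The section on controls names no corresponding outcome.

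Three other statements bear on this:

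- **Treatment after IRE:** "Following IRE, patients in this arm will be offered second-line chemotherapy, which is the current standard of care".
- **Treatment of controls:** they receive further chemotherapy, and "Patients randomised to the control arm who have benefitted from initial chemotherapy with FOLFIRINOX may continue on the same regimen", if the oncologist thinks it appropriate.
- **Imaging:** "All patients will be clinically reviewed every 3 months during which a CT CAP will be performed".

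Elsewhere in the Outcomes section, health resource costs are explicitly for both arms and overall survival runs from randomisation. The Abstract says that the data are likely to guide the primary outcome measure and the power of a later trial.

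**The concern.** Patients in the IRE arm get IRE and are also offered chemotherapy; controls get chemotherapy. A rate seen only after IRE reflects both treatments, together with the selection of patients who reached the procedure. The article's own discussion of why systemic chemotherapy comes first says that it can make some unresectable tumours resectable, so a conversion seen after IRE need not be due to IRE.

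The Discussion argues for a randomised trial because uncontrolled IRE series may reflect patient selection. Reporting these outcomes in one arm brings back that weakness for local control and conversion to surgery, inside a trial that has a randomised control group with the same CT schedule. If the later trial's primary outcome or assumed effect were chosen from these rates, there would be no concurrent rate to set them against.

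**Working it through.** The article gives no target or expected rate for these outcomes, so there is no planned figure to reproduce. The check takes the sample size from the article and uses stated assumptions for the rest.

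**Inputs**
- Patients per arm: 50 randomised equally (Sample size calculation), so 50 / 2 = 25.
- Conversion rate with chemotherapy alone in patients still unresectable after FOLFIRINOX: not given in the article. Assumed 5%, 10% and 15%.

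**1. Conversions expected in the IRE arm if IRE has no effect**

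Expected number = 25 × p. The chance of at least 3 is the binomial tail P(X ≥ 3 | 25, p).

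| Assumed p | Expected of 25 | P(at least 3) |
|---|---|---|
| 5% | 1.25 | 13% |
| 10% | 2.5 | 46% |
| 15% | 3.75 | 75% |

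For example, at p = 10%: 1 − (0.9^25 + 25 × 0.1 × 0.9^24 + 300 × 0.1² × 0.9^23) = 1 − (0.072 + 0.199 + 0.266) = 0.463.

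**2. What a single-arm result would show**

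An observed 4 of 25 (16%) has an exact (Clopper-Pearson) 95% interval of 4.5% to 36.1%. That interval contains 5%, 10% and 15%, so such a result fits no effect of IRE at any of these rates. A narrower interval would not cure this, because there is no control rate to compare with.

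**3. What a comparison of 25 v 25 would show**

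95% half-width of the difference = 1.96 × √(2p(1 − p)/25), with the same underlying rate p in each arm.

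- p = 10%: 1.96 × √(0.18/25) = 1.96 × 0.0849 = 16.6 points.
- p = 25%: 1.96 × √(0.375/25) = 1.96 × 0.1225 = 24.0 points.
- p = 50%: 1.96 × √(0.5/25) = 1.96 × 0.1414 = 27.7 points.

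This is imprecise, but it is a randomised contrast.

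**4. Why the class of deaths should be visible in any such table**

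As an illustration only, suppose that 50% of an arm show growth on a scan and a share d die with no scan showing growth.

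| d | Deaths counted as no growth | Deaths counted as failure | Deaths excluded |
|---|---|---|---|
| 10% | 50% | 40% | 40/90 = 44% |
| 20% | 50% | 30% | 30/80 = 38% |
| 30% | 50% | 20% | 20/70 = 29% |

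The article does not give d. The figures show only that the local-control rate depends on the convention, which should be the same in both arms.

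**The case against.** **The outcomes are descriptive and procedural.** They come under an objective about the practicality and technical success of IRE, for which an IRE-only denominator is natural. The article says that the trial lacks power for effectiveness. The criteria for progress to a full trial use recruitment, consent, technical success and loss to follow-up, none of which is at issue here. Overall survival, PFS and quality of life are listed without restriction to one arm. All of this stands and keeps the point modest. It does not remove it: PFS, as usually defined, combines local progression, distant progression and death, so it isolates neither local control nor conversion to surgery.

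**The comparison would be imprecise.** That is true, at about 17 to 28 points, and is a reason to present it as descriptive.

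Three stronger readings are tempting, and the article does not support them:

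- *The plan counts deaths as successes.* The success rule follows a sentence on assessing follow-up CT scans, and the article is silent on patients who die without a scan showing growth. That rule is commonly left to the analysis plan, which is not shown. A count of all deaths by 12 months would not measure the problem either, since only deaths without prior imaged growth matter.
- *Controls can be expected to reach the 25.9% resection rate quoted in the Introduction.* That figure describes patients undergoing first-line FOLFIRINOX. The trial enrols those still unresectable after it, so patients already converted have been removed.
- *The Pancreas IRE section contradicts itself on growth.* It names follow-up success, judged by enlargement or greater vascularity, and local disease control by RECIST at the end of follow-up. The two carry different labels and can coexist.

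**Conclusion.** The point holds as a limited improvement to the comparison. Local-growth success, eligibility for surgery and R0/R1 rates are defined only after IRE, in a trial where both arms can receive chemotherapy and have the same 3-monthly CT. As worded, these proportions cannot separate IRE from chemotherapy: with no IRE effect, 1.25 to 3.75 conversions would be expected among 25 IRE patients at assumed rates of 5% to 15%. The conclusion about attribution rests on the design and not on those assumed rates, which only illustrate its size.

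The consequence is a lost opportunity. The primary outcome and the progression criteria are unaffected, and the scans needed for the comparison are already scheduled in both arms.

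**What to change.** Report the following in both arms, from randomisation, with all randomised patients as denominator and at a fixed time such as 12 months:

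1. eligibility for surgery;
2. resection performed, with R0/R1 status;
3. local progression, by one RECIST-based definition.

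Show deaths without documented local growth as a separate category, or as a competing event, and not as local control. Give the difference between arms with its 95% confidence interval, labelled as descriptive. Keep the IRE-only success rate as a descriptive procedural outcome.

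The cost is applying the planned RECIST reading, with its central review, to control CTs already taken, and a little more tabulation. No new scans or patients are needed.

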### Follow-up

All patients will be clinically reviewed every 3 months during which a CT CAP will be performed. Additional imaging can be performed if clinically indicated. Other investigations will include biochemistry and haematology, CA19–9 levels, C Reactive Protein (CRP), QoL as measured by a validated questionnaire (EQ5D-5L)^28^ and a clinical review of any AEs experienced. This information will be recorded in an electronic case report form.

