### Complications of pancreas IRE therapy

Reported complications following pancreas IRE include pancreatic fistula, venous and arterial thrombosis, arterial pseudoaneurysm and pancreatic abscess.^14^ The mean morbidity rate in the studies examined is 34% but can reach up to 62%.^20^ The average rate of severe complications (defined as greater than grade III on the Clavien-Dindo scale) following IRE is 8% but can be as high as 44%.^21^ The average procedure of related mortality rate in these studies is 3%.^12^

There are significant variations in the percentage and severity of complications reported. This difference may be due to the case selection, whether IRE is carried out during surgery (via an open or laparoscopic approach) or with image guidance in the interventional radiology (IR) suite, the treatment algorithm, the completeness of reporting from treatment centres or the experience of the radiologist and/or centre. Only two studies specifically mention the experience of clinicians delivering IRE^16 22^ and, currently, there is limited published data available exploring the number of IRE procedures performed and the relationship with outcomes.^23^

IRE is a palliative option and, therefore, its impact on patient’s quality of life (QoL) is an essential consideration. A single-centre prospective study evaluating the QoL pre and post-IRE in patients with LAPC demonstrated that IRE had no adverse effect on QoL in the short-term; however, concomitant treatment with chemotherapy after IRE as well as other inter-related factors may confound the results.^24^ We were unable to find any studies comparing QoL changes following IRE to a control group. The published data, to date, regarding the improvement in QoL in patients with LAPC undergoing IRE is weak and needs further exploration.

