**Figure 1 F1:**
[figure not shown]
Trial flow diagram. CTCAP, CT chest abdomen pelvis; FOLFIRINOX, 5-FluoroUracil, Leucovorin, Irinotecan and Oxaliplatin; IRE, irreversible electroporation; LAPC, Locally Advanced Pancreatic Cancer; OS, overall survival; PFS; progression free survival; QoL, quality of life; SoC, standard of care; sMDT, specialist multidisciplinary team.

**Table 1 T1:** Schedule of enrolment, interventions and assessments of the LAP-PIE trial

Timepoint	Study period									
	Enrolment	Allocation	Post-allocation follow-up time points							Close-out
	-*t_1_*	0	*Pre-IRE*	*6 hours post-IRE*	*6 days post-IRE*	*3 months*	*6 months*	*9 months*	*12 months*	
Enrolment:										
Eligibility screen	X									
PIS given	X									
*Systemic treatment with FOLFIRINOX*	X									
*sMDT*	X									
*Informed consent*	X									
Allocation		X								
Interventions:										
*IRE (intervention)*										
*Systemic chemotherapy (SoC)*										
Assessments:										
*CT CAP*	X					X	X	X	X	
*Blood tests*	X		X	X	X	X	X	X	X	X
*HRQoL*						X	X	X	X	X
*Complications*						X	X	X	X	X

CT CAP, CT chest abdomen pelvis; FOLFIRINOX, 5-FluoroUracil, Leucovorin, Irinotecan and Oxaliplatin; HRQoL, health-related quality of life; IRE, irreversible electroporation; LAP-PIE, locally advanced pancreatic cancer with percutaneous irreversible electroporation; PIS, patient information sheet; sMDT, specialist multidisciplinary team; SoC, standard of care.

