### Sample size calculation

Formal sample size calculations are not appropriate for a feasibility study. Sample sizes between 24 and 50 have been recommended to estimate the SD required for a sample size calculation to allow for the design of a subsequent RCT aimed at evaluating the cost-effectiveness of IRE in patients with LAPC.^29 30^ A convenient sample size of 50 patients, randomised equally to the two groups, has been selected.

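### Table 1 schedules no EQ-5D-5L before randomisation, so change from baseline, baseline-adjusted comparisons and the baseline/follow-up correlation cannot be estimated

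*Protocol article*

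**What the plan says.** Table 1 of the protocol article, titled "Schedule of enrolment, interventions and assessments of the LAP-PIE trial", has columns for enrolment, allocation, pre-IRE, 6 hours and 6 days after IRE, 3, 6, 9 and 12 months, and close-out. The HRQoL row is marked at 3, 6, 9 and 12 months and close-out only. The CT row is marked at enrolment and at the four 3-monthly visits. The blood-test row is marked at enrolment, at the three peri-procedural times and at every later time.

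The Follow-up section says "All patients will be clinically reviewed every 3 months during which a CT CAP will be performed", and names the instrument among the other investigations at those reviews: "QoL as measured by a validated questionnaire (EQ5D-5L"). No section mentions a quality-of-life value at baseline. The Translational study section, by contrast, does state a baseline for the immune markers.

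On the role of the measure, the Outcomes section says that "outcome measures including OS (measured from randomisation), PFS and QoL will be evaluated". The section on complications of pancreas IRE says that, because IRE is palliative, its impact on patients' "quality of life (QoL) is an essential consideration". It adds that the authors found no study comparing quality-of-life change after IRE with a control group. The Sample size calculation section says: "Sample sizes between 24 and 50 have been recommended to estimate the SD required for a sample size calculation". It does not name the variable whose SD is meant.

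**The concern.** A randomised trial with a chemotherapy-alone arm could begin to fill the gap the article describes, namely how quality of life changes after IRE relative to controls. Change needs a starting value, and the schedule provides none. Because the trial is open label, a score taken once the patient knows the allocation may be influenced by it. The value therefore has to be collected before randomisation and cannot be reconstructed afterwards.

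Four things are lost:

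- change from baseline;
- a comparison of arms adjusted for baseline;
- the ability to see a chance imbalance at entry with 25 patients per arm;
- the design parameters that need paired measurements (change-score SD, baseline-adjusted SD and baseline/follow-up correlation).

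The last matters because the trial is meant to supply the information for designing a larger one. If that trial estimates QALYs for cost-effectiveness, data collected on the present schedule would also lack the starting utility.

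**Working it through.** **Is the blank real?** Each row of Table 1 was aligned to the header. The CT, blood-test and HRQoL rows all have the same number of fields as the header (11). The CT and blood-test marks fall where expected, including at enrolment. The HRQoL row is blank in all five columns before 3 months, so the gap is not a shift of columns in the extracted text.

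**Is there a planned figure to reproduce?** Not for quality of life. The article gives no SD, correlation, effect size, alpha or power for EQ-5D-5L. The 50 is a convenience number ("A convenient sample size of 50 patients, randomised equally to the two groups, has been selected"). It agrees with the recruitment arithmetic under Assessment of feasibility: 40 eligible × 20% × 5 centres × 15/12 years = 50. The figures below therefore illustrate consequences under stated assumptions.

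**Precision.** With equal variances and a baseline/follow-up correlation ρ, adjusting for baseline multiplies the variance of the arm difference by 1 − ρ², a reduction of ρ²:

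- ρ = 0.3: 0.09, or 9%
- ρ = 0.5: 0.25, or 25%
- ρ = 0.7: 0.49, or 49%

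**What this means for sizing the full trial.** Assume a standardised effect of 0.4, two-sided 5% and 90% power. Then n per arm = 2(1.960 + 1.282)² × k / 0.4², where k = 1 for follow-up score alone, 1 − ρ² for baseline-adjusted analysis and 2(1 − ρ) for change scores.

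| Analysis | ρ = 0.3 | ρ = 0.5 | ρ = 0.7 |
|---|---|---|---|
| Follow-up score alone | 132 | 132 | 132 |
| Adjusted for baseline | 120 | 99 | 67 |
| Change score | 184 | 132 | 79 |

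The planned schedule cannot estimate ρ, so it cannot say which column applies.

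**What remains estimable.** The SD of the score at a given follow-up visit needs no baseline. With both arms pooled (n − 2 degrees of freedom), the 95% limits are about 0.83 to 1.25 times the estimate with 50 patients. With 45 patients (50 less the 10% loss in the progression criteria) they are 0.83 to 1.27.

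**Chance imbalance.** With 25 per arm, the standard error of the baseline difference is √(2/25) = 0.283 SD. An imbalance of at least 0.5 SD corresponds to z = 0.5/0.283 = 1.77, a two-sided probability of 0.077. It is unlikely, but under this schedule it would be neither seen nor adjusted for.

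**QALY implication for the later trial.** In trapezoidal arithmetic the starting utility carries weight 0.25/2 = 0.125 years. An error of 0.05, 0.10 or 0.20 in an assumed starting value moves a patient's QALY by 0.006, 0.0125 or 0.025. An error common to both arms cancels from the difference; an unmeasured imbalance between arms does not.

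**The case against.** The case on the other side is substantial.

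First, a reader might infer that the SD for the next trial cannot be estimated at all. The article does not support that. It does not say which SD it means, and the SD of follow-up scores is available and can size a trial analysed on those scores. Only the quantities that need paired values are lost.

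Second, a reader might treat missing QALYs as a failure of this trial. The article names neither QALYs nor change scores as analyses, describes its costs as indicative, and leaves cost-effectiveness to the subsequent trial. The QALY point is an implication for that trial, and the weight of the missing value is one-eighth of a year.

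Third, randomisation keeps a comparison of follow-up scores valid without a baseline, apart from attrition, which a baseline score would not prevent. The cost is in precision and in exposure to chance imbalance. At a correlation of 0.3 the precision cost is only 9%.

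Fourth, a baseline score would not reveal an early dip after IRE. A line drawn from baseline to 3 months would pass over it.

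Fifth, the Follow-up section alone proves little. It also lists biochemistry and haematology without a baseline, yet Table 1 has enrolment bloods. The article is condensed, and the intervention rows of Table 1 appear blank in the text as read.

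The first four points stand and limit the finding. The fifth does not remove it. The HRQoL row is a positive schedule with its own marks, and it starts at 3 months. If the full protocol does collect a baseline, the published table needs correcting; if not, the design needs amending.

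**Conclusion.** The concern holds in a limited form. As published, the schedule has no pre-randomisation EQ-5D-5L. It therefore cannot yield change from baseline, a baseline-adjusted comparison, or the change-score SD, adjusted SD and baseline/follow-up correlation. Follow-up SDs and an unadjusted randomised comparison survive.

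The variance reduction forgone is 9% to 49% for correlations of 0.3 to 0.7. That range is assumed, as are the effect size and power behind the sample sizes shown.

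A reader might conclude that the trial's main result is compromised. It is not. The primary outcome is recruitment, screening failures, pathway completion and withdrawal. The progression criteria are recruitment, consent rate, technical success and loss to follow-up. None depends on quality of life. This is a worthwhile and inexpensive correction to a secondary outcome. It should be made early, because the value cannot be recovered for patients already randomised.

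**What to change.** In Table 1, add an HRQoL mark at enrolment, and say in the text that EQ-5D-5L is completed after consent and before randomisation in both arms. Analyse quality of life at follow-up with the baseline score as a covariate. Report the baseline/follow-up correlation and the baseline-adjusted SD, alongside the unadjusted follow-up SD, for the design of the full trial. If the full protocol already schedules this measurement, correct the published table to match.

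The cost is one short questionnaire at a contact that already takes place, and a minor amendment. Patients randomised before the amendment would have no baseline value, and the report should give their number. If the early weeks after IRE are of interest, the baseline score alone will not describe them; that would need a separate decision on an additional assessment time.
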